**Methods/design:**

This paper presents a double-blind, double-dummy, randomized controlled trial. After a 2-week run-in period, 80 AR patients with LSQDS will be recruited and randomly allocated to the BMF group or the control group in a 1:1 ratio. The patients in the BMF group will receive BMF and the placebo for levocetirizine hydrochloride orally, while the control group participants will receive levocetirizine hydrochloride and the placebo for BMF orally. All participants will receive 4 weeks of treatment and 12 weeks of follow-up.

The primary outcome is a change in the Total Nasal Symptom Score (TNSS). Secondary outcomes include changes in scores for the standard version of the Rhinoconjunctivitis Quality of Life Questionnaire (RQLQ(S)), and visual analog scale (VAS); changes in serum levels of the cytokines interleukin-4, interferon-γ, transforming growth factor β-1, and interleukin-17; and changes in the gut microbiota composition in the stool. The TNSS, RQLQ(S), and VAS will be recorded at the beginning of, middle of and after the treatment period and at the end of each month in the 3-month follow-up period. Blood and stool samples will be collected at baseline and the end of the treatment. The aforementioned four cytokines will be detected in the serum using enzyme-linked immunosorbent assays, and the stool gut microbiota will be detected using 16S ribosomal ribonucleic acid sequencing. Any side effects of the treatment will be recorded.

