### Blinding

The research team members, with the exception of the clinical research methodology personnel and eligible participants, will be blinded to the treatment allocation. The study code will not be revealed until the end of the study, unless there is a serious adverse event (AE).

This study is a double-blind, double-dummy RCT, and the medicine used for treatment and the placebo will be identical in appearance. In addition, the research team will be instructed not to communicate with the participants regarding their possible treatment group allocation.

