### Outcome measurement

The primary outcome is a change in the Total Nasal Symptom Score (TNSS) [40]. Secondary outcome measures are as follows: (1) changes in the standard version of the Rhinoconjunctivitis Quality of Life Questionnaire (RQLQ(S)) score; (2) the frequency of AR episodes and their severity (visual analog scale, VAS); (3) changes in the serum levels of cytokines IL-4, interferon-γ (IFN-γ), transforming growth factor β-1 (TGF-β1), and interleukin-17 (IL-17), and changes in the gut microbiota composition in stools before and after treatment. In addition, participants will complete a medicine diary and report any AEs related to the intervention drugs throughout the trial.

The TNSS evaluates the following four nasal symptoms: rhinorrhea, nasal obstruction, nasal itching, and sneezing. The symptoms are self-assessed and recorded by subjects using a four-point scale (0 = no symptoms, 1 = mild symptoms, 2 = moderate symptoms, and 3 = severe symptoms), with low scores indicating less severe nasal symptoms [40]. The RQLQ(S) is a disease-specific questionnaire that can assess quality of life impairment in AR patients. This questionnaire consists of 28 questions covering the following seven domains: activities, sleep, non-nose/eye symptoms, practical problems, nasal symptoms, eye symptoms and emotional problems [41]. The RQLQ(S) with standardized activities is an updated version of the original RQLQ [42]. It has been translated into different languages and has frequently been used in different countries. The VAS, which ranges from 0 (nasal symptoms not at all bothersome) to 10 (nasal symptoms extremely bothersome) was designed to assess the severity of nasal symptom disturbance and has been validated for use in the quantitative evaluation of AR severity [43]. The TNSS, RQLQ(S), and frequency and severity of AR episodes will be evaluated at the beginning of, middle of and after the treatment period and at the end of each month during the 3-month follow-up period (Fig. 2).

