### Quality assurance and data management

To ensure strict adherence to the study protocol and familiarity with the trial administration process, an independent steering committee will be formed by the principal investigator prior to the beginning of the study. This committee will be composed of one independent chairman ([name]), [name], [name], and two other independent members, including at least one patient and a public involvement representative. The responsibilities of the steering committee will include approving any amendments to the main study protocol, monitoring the trial, and approving and commenting on project deliverables. The entire research team will then be provided with a standard operating manual detailing the procedures and will be required to undergo training.

All information from CRFs will be carefully recorded. All errors will need to be crossed out and corrected, after which the correction must be signed and dated by the participant or researcher. Patient withdrawals or missed follow-up visits will be recorded in the CRFs. An independent Data Monitoring Board will be established at the beginning of the study and will be composed of four fully independent members: a chairman, an otolaryngologist, a biostatistician and a clinical pharmacology expert from the GDPHCM. The Data Monitoring Board will review and oversee all the source documents and CRFs. The essential information (consent information, enrollment, number and proportion of missed visits, patients lost to follow-up, and AEs) will be monitored and evaluated for completeness and accuracy.

Data will be entered using the double-entry method, and to decrease errors, the data will be checked regularly by the research assistants and overseen by the monitors. Research assistants will double check the data before logging them and will promptly notify the research team if any discrepancies are found. All modifications will be marked on the CRFs. The database will be locked after all the data have been cleaned. If a participant withdraws from the trial either during the treatment period or the follow-up phase, the reasons will be clarified and the rate of participant withdrawal or loss to follow-up will be analyzed statistically.

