### Criteria for stopping treatment

A participant may stop treatment and withdraw from the research project for any reason at any time, and the reason for the withdrawal will be recorded in their CRF. The participants will be told that they have the right to withdraw from the trial and that they will be provided with standardized treatment if they withdraw.

The criteria for stopping treatment and withdrawing from the research project are:The participant has suffered an AE related to taking the drug, and the investigator believes it is not appropriate for them to continue taking the drug.The participant is diagnosed with asthma or other complications of AR during the study.The participant develops another severe disease that needs to be treated during the study.Poor compliance, such that the actual drug usage is less than 80% or more than 120% of the prescribed dose.Use of drugs proscribed for AR during the study.

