## Discussion

Although treatment for AR has been developed and standardized, the symptoms of some AR patients are still not well controlled with current pharmacological therapies [47, 48]. CHM, which may have an effect on AR, has gradually received increasing attention and has been adopted for the treatment of AR [8]. Syndrome differentiation or pattern identification is a specific analysis of individual body constitutions, symptoms, and signs based on TCM physiology and pathology and is performed before arriving at a diagnosis or drawing a conclusion [49]. This step must be performed before prescribing CHM formulas because accurate syndrome differentiation or pattern identification ensures accurate therapeutic effects with fewer AEs [8]. BMF is composed of modified *bu zhong yi qi tang* and *yu ping feng san*, which are typically applied to treat allergic diseases [17]. Based on previous experience with the use of BMF to treat AR, this study combines syndrome differentiation and treatment with strict RCT design principles to assess the efficacy and safety of BMF for the treatment of AR. Regarding the mechanistic study of this formulation, this study aims to determine whether BMF can modulate cytokine levels and gut microbiota.

To the best of our knowledge, this is the first double-blind double-dummy RCT aimed at determining the efficacy of BMF in treating AR patients with LSQDS. This is also the first study to investigate changes in inflammatory cytokines as well as changes in the gut microbiota with CHM-based therapy.

There are limitations to this study. The first is a lack of validated outcome measures to evaluate the body constitution of AR patients with LSQDS. In Chinese medicine theory, the body constitution of a patient is dynamic and may change after the BMF intervention. The second limitation is that the sample size calculation was based on a previous study [46] and our clinical observations; thus, the sample size of our study may have been different if more cases had been observed by a prior rigorous RCT. The last limitation is that this study explores only the mechanism by which the BMF formula treats AR and does not address the mechanism at a component level.

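### Participants' adverse event reports are conditioned on relatedness to the study drugs, which under-records harms before any investigator judges causality

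*Protocol article*

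**What the plan says.** All places are in the protocol article.

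- **Outcome measurement:** participants keep a medicine diary and "report any AEs related to the intervention drugs throughout the trial". This is the only collection rule for harms that the article states.
- **Abstract, Methods/design:** "Any side effects of the treatment will be recorded". The framing is again causal, and no reporter is named.
- **Quality assurance and data management:** the Data Monitoring Board reviews source documents and case report forms (CRFs). The essential information listed there ends with "patients lost to follow-up, and AEs) will be monitored and evaluated for completeness and accuracy". No relatedness qualifier appears.
- **Criteria for stopping treatment:** the investigator's judgement is described only for an AE already taken to be drug-related, and concerns whether the drug is continued. Reasons for withdrawal go in the CRF.
- **Blinding:** "This study is a double-blind, double-dummy RCT, and the medicine used for treatment and the placebo will be identical in appearance".
- **Discussion:** the trial is presented as using "strict RCT design principles to assess the efficacy and safety of BMF for the treatment of AR". The abstract's Background adds that direct evidence on BMF's efficacy and safety is lacking.

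Nowhere does the article provide for collecting events whatever their cause, or say who judges relatedness.

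**The concern.** An adverse event is normally recorded first and attributed afterwards. Here attribution is written into the act of reporting, and the person reporting is a layperson taking both an eight-herb granule and an oral solution, one of them a placebo. Such a participant has little basis for deciding whether a symptom comes from a study drug. An effect that nobody expects is the least likely to be attributed and so the least likely to be reported. For a formula without direct safety evidence, those are the informative events.

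At stake is what the safety table will mean. Counts of events that participants thought were related are smaller than total adverse events and could be read as reassurance. The unqualified wording in the quality assurance section also leaves it unclear which of the two quantities is being monitored.

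**Working it through.** **Plan's own figure.** The plan gives no adverse event rate and no safety power, so there is nothing to reproduce on this point. The only input taken from it is 40 participants per arm (Sample size calculation). The sample size itself is unaffected. Event risks *p* and capture probabilities *q* (the share of true events that the participant attributes and reports) are assumptions throughout.

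**1. What zero reports can exclude.** With *n* = 40 and no events, the one-sided 95% upper limit on the recorded risk is 1 − 0.05^(1/40) = 7.2%. The recorded risk is *q*·*p*, so the limit on the true risk is 7.2%/*q*:

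| Capture *q* (assumed) | Upper limit on true risk |
|---|---|
| 1 | 7.2% |
| 0.5 | 14.4% |
| 0.25 | 28.9% |

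The 7.2% follows from *n* = 40 alone and would apply under any wording. Only the increase above it is due to incomplete capture.

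**2. Chance of seeing an event at all.** P(at least one in 40) = 1 − (1 − *qp*)^40. For an assumed true risk of 5%:
- *q* = 1: 1 − 0.95^40 = 87%
- *q* = 0.5: 1 − 0.975^40 = 64%

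**3. Equal capture in both arms.** Expected reports are 40·*p*·*q*. Assume true risks of 30% and 15%. Power is the two-sided 5% normal approximation, Φ[(|d| − 1.96·SE0)/SE1], where d is the risk difference, SE0 its pooled standard error and SE1 its unpooled standard error.

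| *q* in both arms | Expected reports | Risk difference | Risk ratio | Power |
|---|---|---|---|---|
| 1 | 12 vs 6 | 0.15 | 2.0 | 36% |
| 0.7 | 8.4 vs 4.2 | 0.105 | 2.0 | 25% |
| 0.5 | 6 vs 3 | 0.075 | 2.0 | 18% |

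The risk difference shrinks in proportion to *q* and power falls, but the ratio does not move.

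**4. Unequal capture.** Same assumed true risks, true ratio 2.0:
- *q* = 0.5 and 0.8: 40 × 0.30 × 0.5 = 6 vs 40 × 0.15 × 0.8 = 4.8, ratio 1.25
- *q* = 0.8 and 0.5: 9.6 vs 3, ratio 3.2

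Unequal capture does not require unblinding. Two different active drugs can cause different kinds of event, and familiar kinds may be attributed more readily. If both arms had a true risk of 20% (8 events each), with capture 0.4 for unfamiliar BMF events and 0.8 for recognised control events, reports would be 40 × 0.2 × 0.4 = 3.2 vs 40 × 0.2 × 0.8 = 6.4, a ratio of 0.5 where the truth is 1. Reversing the capture rates gives a ratio of 2. Nothing in the article says which, if either, applies.

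**5. Whether other sections close the gap.** The Board can check source documents and CRFs, and a severe new disease, an AR complication or a withdrawal has a recording route of its own. None of these routes reaches a non-severe event that a participant stayed on treatment with and did not report.

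**The case against.** The strongest reply is that a condensed article is being read too closely. Event definitions, elicitation and grading usually sit in the full protocol, the CRF and the operating manual that the quality assurance section mentions. That holds for detail that is absent. It does not hold for a rule that the article does state, and which conflicts with its own unqualified wording elsewhere.

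Several stronger readings are tempting, and the documents do not support them:

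- **That unrelated events are barred from the CRF.** A reader might infer that only related events may be recorded. The text does not say so. The word only is an inference from the reporting sentence, and the quality assurance section lists AEs without restriction.
- **That the filter acts before any blinded assessment.** In a double-dummy trial the participant's own judgement is meant to be blinded. One sentence in Blinding ("with the exception of the clinical research methodology personnel and eligible participants, will be blinded to the treatment allocation") can be read as excepting participants, but the design label and the matched placebos point the other way. What the filter precedes is investigator assessment.
- **That the comparison is biased towards too few harms on BMF, or is no longer randomized.** Reports compared by randomized arm remain a randomized comparison of reports. Equal filtering leaves the ratio intact, and unequal filtering can move it either way.
- **That oversight sees only the CRF.** The Board also reviews source documents.

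It is also fair that the objectives at the end of the Background name efficacy and mechanism, with safety appearing as an aim in the Discussion, and that Data analysis describes no specific adverse event comparison. This limits the consequence but does not remove it, because the trial still says it will assess safety.

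**Conclusion.** The point holds as one of under-recording. The single stated collection rule makes relatedness a condition of the participant's report, the abstract shares that framing, and the quality assurance section does not. Applied literally, the rule lowers event counts, risk differences and precision, and weakens any statement that an event was not seen. A directional bias between arms is possible but not shown.

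In size, zero of 40 excludes rates above 7.2% with full capture and only above about 14% at half capture. The first figure is exact for *n* = 40. The second, like every other illustration above, rests on an assumed capture rate for which the documents give no basis. The primary outcome and the sample size are untouched. The point deserves correction because the remedy is cheap and safety is a declared purpose of the trial.

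**What to change.** Reword Outcome measurement so that participants record every adverse event regardless of suspected cause, and the blinded investigator then judges severity and relatedness. Tabulate all adverse events by randomized arm as the main safety display, with related events in a secondary table. Bring the abstract and the quality assurance section into line, so that all three refer to the same quantity.

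The cost is wording, a diary and CRF field, and slightly more recording work.

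Timing limits what can be recovered. Trial status reports 76 recruited and 40 completed by 7 November 2017. Run-in, treatment and follow-up take 2 + 4 + 12 = 18 weeks, so someone recruited on that date and following the schedule would finish by about 13 March 2018, before the article's publication on 18 January 2019. If the CRF and diary did collect all events, the sponsor need only say so and correct the sentence. If they collected related events only, missed events cannot be recovered: the report should state this as a limitation and should not present those counts as total adverse events.

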### Quality assurance and data management

To ensure strict adherence to the study protocol and familiarity with the trial administration process, an independent steering committee will be formed by the principal investigator prior to the beginning of the study. This committee will be composed of one independent chairman ([name]), [name], [name], and two other independent members, including at least one patient and a public involvement representative. The responsibilities of the steering committee will include approving any amendments to the main study protocol, monitoring the trial, and approving and commenting on project deliverables. The entire research team will then be provided with a standard operating manual detailing the procedures and will be required to undergo training.

All information from CRFs will be carefully recorded. All errors will need to be crossed out and corrected, after which the correction must be signed and dated by the participant or researcher. Patient withdrawals or missed follow-up visits will be recorded in the CRFs. An independent Data Monitoring Board will be established at the beginning of the study and will be composed of four fully independent members: a chairman, an otolaryngologist, a biostatistician and a clinical pharmacology expert from the GDPHCM. The Data Monitoring Board will review and oversee all the source documents and CRFs. The essential information (consent information, enrollment, number and proportion of missed visits, patients lost to follow-up, and AEs) will be monitored and evaluated for completeness and accuracy.

Data will be entered using the double-entry method, and to decrease errors, the data will be checked regularly by the research assistants and overseen by the monitors. Research assistants will double check the data before logging them and will promptly notify the research team if any discrepancies are found. All modifications will be marked on the CRFs. The database will be locked after all the data have been cleaned. If a participant withdraws from the trial either during the treatment period or the follow-up phase, the reasons will be clarified and the rate of participant withdrawal or loss to follow-up will be analyzed statistically.

The study will be monitored by the Scientific Research Department and Ethics Committee of GDPHCM, which is independent of both the investigators and the sponsor. Interim auditing will include off-site surveillance and the submission of a report about the progress of the study.

### Sample size calculation

This study is mainly focused on determining the efficacy of BMF for AR patients with LSQDS. The primary outcome is the TNSS. With reference to data from a previous study [46] and our clinical observations, the sample size was calculated using the noninferiority test for two means with software PASS 2011. We assumed that the TNSS of the treatment group will be 5.53 ± 2.79 and that of the control group will be 6.64 ± 3.06. To obtain a significance level of 5%, a power of 90%, and a noninferiority margin of 0.92, 74 participants are required. Allowing for an 8% dropout rate, 80 participants are needed, with 40 in each group.

### Criteria for stopping treatment

A participant may stop treatment and withdraw from the research project for any reason at any time, and the reason for the withdrawal will be recorded in their CRF. The participants will be told that they have the right to withdraw from the trial and that they will be provided with standardized treatment if they withdraw.

The criteria for stopping treatment and withdrawing from the research project are:The participant has suffered an AE related to taking the drug, and the investigator believes it is not appropriate for them to continue taking the drug.The participant is diagnosed with asthma or other complications of AR during the study.The participant develops another severe disease that needs to be treated during the study.Poor compliance, such that the actual drug usage is less than 80% or more than 120% of the prescribed dose.Use of drugs proscribed for AR during the study.

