Radix paeoniae alba (*bai shao*)	11.8	5	10	TCM: 1. Nourishing blood and constraining *yin*. 2. Emolliating the liver and relieving pain Pharmaceutical study: 1. Analgesic effect. 2. Antimicrobial and anti-inflammatory effect. 3. Immunologic effect
Herba ecliptae (*mo han lian*)	11.8	5	10	TCM: 1. Enriching the *yin* of the kidney and the liver. 2. Cooling the blood and stopping bleeding Pharmaceutical study: 1. Enhancing immunity. 2. Protecting the liver. 3. Antimutagenic activity
Radix bupleuri (*chai hu*)	11.8	5	10	TCM: 1. Releasing the exterior and abating fever. 2. Soothing liver-*qi* stagnation. 3. Increasing *yang qi* Pharmaceutical study: 1. Inhibiting the central nervous system. 2. Anti-inflammatory and antimicrobial effects. 3. Enhancing immunologic function. 4. Protecting the liver
Xanthii fructus (*cang er zi)*	11.8	5	10	TCM: 1. Dispersing wind and cold. 2. Dispelling dampness. 3. Relieving nasal congestion. 4. Relieving pain Pharmaceutical study: 1. Relieving nasal symptoms. 2. Antimicrobial activity. 3. Preventing coughing
Radix et rhizoma glycyrrhizea (*gan cao*)	5.9	2.5	5	TCM: 1. Tonifying the spleen and replenishing *qi*. 2. Dispelling phlegm and suppressing coughing. 3. Relaxing tension and relieving pain. 4. Clearing heat and detoxifying. 5. Harmonizing medications Pharmaceutical study: 1. Protecting the digestive system. 2. Antiallergic and anti-inflammatory effects

If a participant cannot take the medication for any particular reason, a record will be made, and the medicine will be conserved and returned to the researchers at the end of the study. Two follow-up telephone visits will be performed during the treatment period. Participants who complete treatment will be followed up three times over the course of 3 months (Fig. 2). No other treatment for AR will be allowed for any participant in either group during the study period. The rescue medication, desloratadine tablets (5 mg orally every night, Hainan Poly Pharmaceutical Co., Ltd., Chinese State Food and Drug Administration approval number: H20040972), will be provided for participants who may experience AR episodes. Administration of the rescue medication will be recorded and statistically analyzed as an indicator of a curative effect.

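### Drug-related adverse events, poor compliance and proscribed rhinitis drugs end study participation as well as study drug, which undermines the stated intention-to-treat analysis

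*Protocol article*

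**What the plan says.** In the Protocol article, the section Criteria for stopping treatment introduces its list with "The criteria for stopping treatment and withdrawing from the research project are". Among the five entries are a drug-related adverse event after which the investigator considers further dosing inappropriate; "Poor compliance, such that the actual drug usage is less than 80% or more than 120% of the prescribed dose"; and "Use of drugs proscribed for AR during the study". The same section tells participants that "they will be provided with standardized treatment if they withdraw".

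Three other sections bear on what happens next:

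- **Interventions:** "Participants who complete treatment will be followed up three times over the course of 3 months". Rescue desloratadine is permitted, and its use is itself an outcome: "Administration of the rescue medication will be recorded and statistically analyzed as an indicator of a curative effect".
- **Quality assurance and data management:** for a participant who withdraws, "the reasons will be clarified and the rate of participant withdrawal or loss to follow-up will be analyzed statistically". Further outcome assessment is not mentioned.
- **Data analysis:** every analysis is to follow intention-to-treat, and missing values are filled with a mean or median taken from participants with complete data.

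**The concern.** Intention-to-treat needs outcomes from patients who stopped, misused or supplemented the study drug. Here those patients are the ones sent out of the study. Conditions that normally define a per-protocol set have become grounds for ending participation.

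These are post-randomization events, and they may be related to outcome: a patient whose nose is badly controlled is more likely to take another drug. If they are related, and the arms lose different numbers, the comparison of BMF with levocetirizine is biased for or against BMF. Who keeps attending is settled while the trial runs, so a later analysis plan cannot repair the loss.

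**Working it through.** **What is lost, by criterion**

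| Criterion | End-of-treatment TNSS | Follow-up scores |
|---|---|---|
| Drug-related adverse event, drug stopped by investigator | can be lost | lost |
| Proscribed rhinitis drug | can be lost | lost |
| Intake outside 80% to 120% | may survive, since compliance may be final only near week 4 | lost |
| Rescue desloratadine | kept; not a withdrawal reason | kept |

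This follows the natural reading of the sections above. The article does not say outright that assessments cease.

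**The plan's own sample size (Sample size calculation section)**

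Inputs: TNSS 5.53 (SD 2.79) for BMF and 6.64 (SD 3.06) for control, margin 0.92, significance level 5%, power 90%.

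- Common SD = √[(2.79² + 3.06²)/2] = 2.928.
- Distance from the margin = 0.92 + (6.64 − 5.53) = 2.03.
- Normal approximation, one-sided 5%: 2 × (1.645 + 1.282)² × 2.928² / 2.03² = 35.6, so 36 per arm (72).
- Noncentral t, one-sided 5%: 37 per arm = 74, as stated. One-sided 2.5% gives 90, so the stated 5% is evidently one-sided.
- Dropout: "Allowing for an 8% dropout rate, 80 participants are needed, with 40 in each group". 74 × 1.08 = 79.9, so 80. This leaves 80 − 74 = 6 patients for all losses, including voluntary withdrawal and loss to follow-up.

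**Size of the bias**

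Simulation with 200,000 runs per case (simulation error about 0.05 percentage points near 5%). Each arm has 40 patients with normal scores and SDs of 2.79 and 3.06. The true difference (BMF minus control) is 0.92, exactly at the margin. The test is a one-sided 5% pooled t test on the patients who remain, with no imputation. Those who leave have the highest values of a variable with correlation ρ to the score. The numbers leaving and ρ are assumptions.

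Each cell gives the mean estimate and the rate of falsely declaring noninferiority.

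| Leaving, BMF vs control | ρ = 0 | ρ = 0.3 | ρ = 0.5 | ρ = 1 (worst scorers leave) |
|---|---|---|---|---|
| none | 0.922; 4.9% | – | – | – |
| 2 vs 1 | 0.923; 4.9% | 0.882; 5.7% | 0.860; 6.2% | 0.801; 8.6% |
| 1 vs 2 | 0.921; 5.1% | 0.968; 4.4% | 0.999; 4.0% | 1.082; 3.8% |
| 4 vs 2 | 0.919; 5.0% | 0.857; 6.0% | 0.817; 7.1% | 0.707; 11.9% |
| 3 vs 3 | 0.920; 5.0% | 0.932; 5.0% | 0.942; 5.1% | 0.960; 6.2% |
| 2 vs 4 | 0.917; 5.1% | 1.006; 3.9% | 1.065; 3.4% | 1.211; 2.8% |

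The standard error of the difference is 2.928 × √(2/40) = 0.65. At ρ = 0.5, the 2 vs 1 case shifts the estimate by 0.92 − 0.86 = 0.06, about 0.09 standard errors.

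**A hazard of keeping everyone**

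Withdrawn patients are promised standardized treatment, and scores on other active treatment can pull the arms together. If k of 40 BMF patients moved fully to the control level, the as-randomized difference would be 0.92 × (40 − k)/40, which is 0.874, 0.851 and 0.828 for k = 2, 3 and 4. The simulation gives 0.876, 0.851 and 0.827, with error 5.7%, 6.2% and 6.6%.

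**The case against.** The strongest reply is that the harmful step is inferred. The article never states that assessments stop, silence in a condensed article is not a rule, and the flow chart and study-period figures cannot be seen here. That justifies caution about the consequence. It does not remove the joint list, which is explicit, and nothing in the text keeps these patients under assessment.

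The effect is also small and its sign unknown. The simulation uses complete cases, whereas the plan imputes, and the losses, their imbalance and the correlation are all assumed. This stands, and it is why the point is rated as modest. How well imputation fills the gaps is a separate issue and is not counted here.

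The remedy carries its own cost. At ρ = 0.3, retention with full convergence does no better than withdrawal (5.7% against 5.7%, and 6.6% against 6.0%). At ρ = 0.5 it gains about half a point (5.7% against 6.2%, and 6.6% against 7.1%). Full convergence is an upper case, but the objection is fair. A per-protocol companion helps only in part, because it leaves out some of the same patients, and requiring both analyses to agree is debatable. The case for collecting the scores does not depend on that rule, since without them neither question can be examined.

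Finally, little may still be open to change. Participation lasts 2 + 4 + 12 = 18 weeks, so the 76 patients recruited by 7 November 2017 would be due to finish by about mid-March 2018, before publication in January 2019. This limits what the change can achieve in this trial. It does not make the rule sound.

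**Conclusion.** The concern holds and should be addressed. As written, the plan ties leaving the study to tolerability, adherence and use of other rhinitis drugs, which conflicts with its intention-to-treat commitment. Patients may still be counted through imputation, so the principle is undermined rather than formally abandoned. The loss falls mainly on follow-up scores and, for adverse-event and proscribed-drug exits, also on the end-of-treatment TNSS.

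In the plausible unequal cases (3 or 6 of 80 leaving, correlation 0.3 to 0.5), the error runs from 3.4% to 7.1% against a nominal 5%. The 11.9% figure is an extreme bound. Confidence is medium, because the end of data collection is a natural reading and the size rests on assumptions.

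**What to change.** - **Criteria for stopping treatment:** keep the list for stopping study drug only, and add: *A participant who stops or misuses study drug, or uses another AR drug, stays in the study and completes all scheduled TNSS, RQLQ(S) and VAS assessments unless consent is withdrawn.* The right to withdraw voluntarily is unchanged.
- **Interventions:** extend the three follow-up visits from treatment completers to all randomized participants.
- **Data analysis:** analyse everyone as randomized on the observed data. Run a per-protocol analysis alongside (compliant, no proscribed AR drugs), and preferably claim noninferiority only if both agree. Report withdrawals by reason and arm.

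The cost is wording in three sections and some follow-up effort. The assessments are already scheduled and no sample-size figure changes. On the status at 7 November 2017 (76 recruited, 40 completed), the change could help at most 76 − 40 = 36 patients in progress, some of whom may already have withdrawn, plus 80 − 76 = 4 still to enrol, so 40 of 80. For patients already withdrawn, only the paired analyses and the reporting by reason and arm remain possible.
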